### Ethics

This study was submitted and approved for ethical review by IntegReview (protocol HLS-07), an independent institutional review board.

## Results

Recruitment for the trial is expected to begin during the second quarter of 2020, and participants will begin the 8-week intervention as they are recruited and consent to participate in the study. Consequently, the first wave of data collection is expected to be complete approximately 8 weeks after recruitment, with an estimated intervention completion date for all participants in the fourth quarter. We plan to conduct data analysis for postintervention assessments once this initial data collection is complete, and these results may be shared at conferences or submitted for publication while we continue to collect data for the 3-, 6-, and 12-month follow-up assessments. Owing to the high cost associated with this research, we plan to conduct preliminary analyses once 20% of our target sample has completed the 8-week intervention. If we find no trends suggesting Happify Health use predicts primary outcomes, we plan to discontinue the study.

Recruitment, data monitoring for participant safety, data storage, protocol implementation, and research administration (participant follow-up, etc) will be under the purview of EB, GK, JS, and AP as employees of Happify Health. All data analyses will be conducted by JM and IK.

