**Methods:**

This is a randomized controlled trial in which adults with a type 2 diabetes diagnosis, elevated hemoglobin A_1c_ (HbA_1c_) levels (≧7), and moderate to severe depressive symptoms will be randomly assigned to a positive emotion regulation skills intervention group or a sham digital intervention with only psychoeducational content. The study will take place over 14 months, including the 8-week intervention (or control) delivered via a digital therapeutic platform (Happify Health) and follow-up assessments at 3, 6, and 12 months postintervention. Throughout the intervention and for 1 week at each postintervention follow-up, participants will complete daily assessments of diabetes-related distress, diabetes regimen adherence, and mood. Our primary outcome, HbA_1c_, will be self-reported every 3 months throughout the study. Secondary and exploratory outcomes will be assessed at baseline; at 8 weeks; and at 3, 6, and 12 months postintervention.

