### Impact of Mental Health Interventions on Diabetes

Research on the impact of mental health interventions applied specifically to people living with diabetes remains limited. Mindfulness and positive psychology (PP) interventions, which are effective in reducing depression and increasing well-being in the general population [29], have shown promise in improving depression, diabetes-related distress, and HbA_1c_ levels among people with type 1 or 2 diabetes [30]. A recent systematic review showed that such interventions, particularly mindfulness-based interventions, led to improvements in psychological outcomes, including self-efficacy, self-compassion, well-being, mental health–related quality of life, positive affect, stress, diabetes-related distress, depression, and anxiety [30]. Mindfulness-based interventions also appeared to lead to improvements in HbA_1c_ levels, although in some cases, the effects were not observed until 1 or 3 months postintervention [30]. Other research also suggested that mindfulness-based interventions have small to moderate effects on metabolic control [31].

Such interventions appear to be particularly successful when patients have higher baseline levels of diabetes-related distress and when interventions are delivered in a group format, draw on mindfulness-based stress reduction (MBSR), and include home practice assignments [32]. Although few of these studies have included long-term follow-up, there is preliminary evidence that the effects of mindfulness-based interventions on depressive symptoms are maintained, or even stronger, after 6 months [30,32], although they may dissipate after 2 or 3 years postintervention [30]. Some findings also suggest that the effects of mindfulness-based interventions on HbA_1c_ levels may actually be stronger 1 or 3 months postintervention rather than immediately postintervention [30].

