### Participants

This study is an RCT (NCT04068805) with an initial target sample size of 400 participants (200 participants per condition). Recruitment will continue until 400 participants have successfully completed pretesting and have been randomized to condition.

Although previous RCTs using Happify Health had response rates ranging from 56% to 72% for an 8-week posttest [60], as the first attempt to include long-term follow-up of Happify Health users, the level of attrition beyond the 8-week intervention is difficult to estimate. The few previous tests of mental health interventions on people with diabetes that included long-term follow-up reported relatively low attrition for 6-month [35,64] and 12-month [34,65] follow-ups; however, all these studies involved in-person interventions and often included booster sessions, thereby increasing the level of contact with participants and increasing response rates. The levels of attrition are much higher in research using digital interventions [66], although dropout rates are lower in RCTs than in open-access interventions [67]. Consequently, although we predict attrition for long-term follow-ups to be higher in this study than in previous research with in-person interventions, it is unclear what percentage of participants to expect for our 3-, 6-, and 12-month assessments.

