### Primary Outcome: Hemoglobin A_1c_

Participants will self-report their HbA_1c_ levels, a measure of the average blood glucose levels over the past 3 months, 5 times throughout the study: at baseline, week 12 (3 weeks postintervention), week 24 (3 weeks after the 3-month postintervention assessment), week 36 (3 weeks after the 6-month postintervention assessment), and week 57 (at the 12-month postintervention assessment). At each assessment, participants will also report the date when they received this HbA_1c_ reading to verify that it falls in the correct time frame.

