After 8 weeks, participants will be instructed to complete the postintervention assessment; this assessment will be identical to the baseline with the exception of HbA_1c_ assessment, which will occur 3 weeks later via the Happify Health app. After completing this assessment, participants will receive an email instructing them to answer daily questions for 1 week and to remind them that we will contact them again in 3, 6, and 12 months for follow-up assessments and that they should continue to use their assigned version of Happify Health as they see fit. Participants will then receive emails instructing them to complete each of the 3-, 6-, and 12-month assessments, which will also be accompanied by 1 week of daily assessments at each follow-up period. Table 1 provides the schedule of activities. To improve participant retention, participants who do not complete the postintervention, 3-, 6-, and 12-month assessments will also receive a reminder phone call from the research staff.

**Table 1 table1:** Schedule of activities for prescreen, intervention period, and follow-up assessments.

Assessments		Time										
		Prescreen	Week 1: qualifying period	Week 2: baseline and first week of intervention	Weeks 3-9: intervention	Week 10	Week 12	Week 21: 3-month follow-up	Week 24	Week 33: 6-month follow-up	Week 36	Week 57: 12-month follow-up

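### The stop/continue look is triggered by 8-week completion, but HbA1c is first due at week 12, and the undefined 'trend' criterion leaves the false-stop risk anywhere from about 10% to 65% at a modest true effect

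*Protocol article*

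**What the plan says.** The Results section of the protocol article gives cost as the reason for an early look: "we plan to conduct preliminary analyses once 20% of our target sample has completed the 8-week intervention". The consequence follows at once: "If we find no trends suggesting Happify Health use predicts primary outcomes, we plan to discontinue the study". The Participants section sets the target at 400, 200 per condition, so 20% is 80 people, about 40 per arm.

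HbA1c is the sole primary outcome. The Primary Outcome section places its first post-baseline report at week 12, three weeks after the intervention. Under Procedures, the assessment at the end of the 8 weeks repeats the baseline one "with the exception of HbA_1c_ assessment, which will occur 3 weeks later via the Happify Health app". Table 1 agrees: HbA1c is not collected at week 10 and is collected at week 12. Procedures also explains the timing: readings after the intervention should reflect glucose only from its start onward.

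The article attaches no threshold, test or effect size to the look, and it gives no power calculation for the 400.

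**The concern.** The event that starts the look does not produce the data on which the look is meant to decide. A person who has just completed 8 weeks is three weeks short of a first primary reading. If the analysis is run when the 80th person completes, it rests on whichever early enrolees have passed week 12, or on some outcome other than the primary one.

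Separately, absence of a trend is not a decision rule. At about 40 per arm, a directional reading and a p-value reading lead to very different decisions. Until one is fixed, nobody can say what power the trial has. The decision could end the whole trial, including the 12-month follow-up. The Strengths and Limitations section justifies the larger sample by the need to learn whether earlier null findings on glycaemic control came from low power. A stop at 80 people or fewer would not answer that question.

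**Working it through.** **Plan's own figure.** 0.20 × 400 = 80 people, 40 per arm. The 400 itself cannot be reproduced, because no alpha, power, effect size or SD is given.

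**1. How many of the 80 have HbA1c due at the trigger?**

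Inputs: a lag of 3 weeks (Primary Outcome section; Procedures). Accrual duration A is not stated. A June 2020 start (Abstract) and completion of the intervention by all participants in the fourth quarter (Results) imply roughly 5 to 21 weeks. I extend the range to 26 weeks as an assumption. Accrual is taken as even, with everyone enrolled completing.

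The first 80 enrol over 0.2 × A weeks, so the number due is 80 × [1 − 3/(0.2A)], with a floor of 0.

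| Accrual A (weeks) | Time to enrol 80 (weeks) | HbA1c due, of 80 |
|---|---|---|
| 5 | 1.0 | 0 |
| 15 | 3.0 | 0 |
| 20 | 4.0 | 20 |
| 21 | 4.2 | 23 |
| 26 | 5.2 | 34 |

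**2. False-stop risk if all 80 do contribute**

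Assumptions: comparison of two means, normal approximation, SD = 1. The anchor effect is what 200 per arm detects at two-sided 0.05 with 80% power: d = (1.960 + 0.842) × √(2/200) = 0.28. A larger effect, d = 0.5, is shown for range.

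At the look, z has mean d/√(2/40) and variance 1. The mean is 0.28/0.2236 = 1.252, or 0.5/0.2236 = 2.236. The trial stops if z < c, so P(stop) = Φ(c − mean).

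Overall power is P(z at look > c and final z > 1.96). The final z has mean d/√(2/200), which is 2.80 or 5.00, and its correlation with the look is √0.2. Without a look, power is 80% or 99.9%.

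| What stops the trial | c | P(stop), d=0.28 | Power, d=0.28 | P(stop), d=0.5 | Power, d=0.5 |
|---|---|---|---|---|---|
| Wrong-direction estimate | 0 | 10.5% | 74% | 1% | 99% |
| Two-sided p>=0.20 | 1.282 | 51% | 44% | 17% | 83% |
| Two-sided p>=0.10 | 1.645 | 65% | 32% | 28% | 72% |

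In the two p-value rows, a significant result in the wrong direction also counts as a stop.

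**3. A lenient rule, for comparison**

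Stop only if z < −0.5. At d = 0.28, P(stop) = Φ(−0.5 − 1.252) = 4.0% and overall power is 78%. Under no effect, P(stop) = Φ(−0.5) = 31%.

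**The case against.** - **Timing.** The trigger sets the earliest moment for the look, not a data cut, and waiting three weeks is compatible with the text. That is fair, but the article does not say the analysis would wait.
- **Numbers due.** The shortfall shrinks with slow accrual and dropout, because the first 80 completers are then spread over a longer period. At 21 weeks and 56% completion, the lower end of the 8-week response range in the Participants section, the count is 80 × [1 − 3 × 0.56/4.2] = 48. Counting from the week-10 assessment makes the lag 2 weeks and gives 42 of 80 at 21 weeks with full completion. These points stand, yet 32 to 38 of the 80 would still have no reading due.
- **Missing threshold.** Cut-offs often sit in an SAP or full protocol, which are not shown, so a missing cut-off alone would be weak ground. Here, however, the article states a discontinuation rule and ties it to the wrong visit.
- **Stopping often.** A reader might infer that the rule would often end a trial of an effective intervention. The document does not support that as a flat statement: it gives no threshold or effect size, and under a directional reading the risk is about 10% at d = 0.28 and 1% at d = 0.5.
- **Usage.** A reader might take the criterion to be an association with amount of use. Elsewhere (Objectives, Strengths and Limitations) the article uses the same phrase for the intervention itself, and the Analysis Plan names frequency of usage separately, so I do not press this.
- **Delayed effect.** A reader might infer that the look falls where the protocol expects least signal. The Introduction does say of HbA1c that "the effects were not observed until 1 or 3 months postintervention", but only for some cases, and week 12 is already close to one month after the intervention.

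**Conclusion.** The mismatch is in the document's own text: a decision on HbA1c is triggered at 8 weeks, while the first post-baseline HbA1c is due at week 12. Run at the trigger, the look would have about 0 to 34 of 80 primary readings due, given even accrual over 5 to 26 weeks, full completion and a 3-week lag.

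Moving the trigger does not settle the criterion. With all 80 contributing, the false-stop risk at d = 0.28 runs from about 10% to 65% over the three readings examined, and overall power from about 74% down to 32%. At d = 0.5 the risk is about 1% to 28%. The effect sizes, unit SD and cut-offs are assumptions. What holds regardless of them is that the readings lead to very different trials. A stop for futility alone does not inflate type I error; what is lost is power.

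**What to change.** 1. Trigger the look when 80 randomised participants have passed their week-12 HbA1c due date, not when 80 have completed 8 weeks.
2. State that it is based on the randomised arm difference in HbA1c.
3. Replace the trend wording with a pre-stated, lenient, non-binding numeric futility rule. One example is to stop only if z < −0.5, that is, clearly in the wrong direction. With 80 contributing, this has about a 4% false-stop risk and 78% overall power at d = 0.28, against 80% with no look, and stops about 31% of the time under no effect.

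The cost is a change of protocol wording, at least three weeks' delay to the look, and a smaller chance of early savings if the intervention does nothing. On that last point, stopping on any wrong-direction estimate would end a trial of an inert intervention half the time (Φ(0) = 50%), against 31% under the example rule. The sponsor should weigh that against the power kept.

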**Results:**

Recruitment is expected to begin in June 2020. Participants will begin the study as they are recruited and will finish in waves. The final wave of data collection from the 8-week intervention is expected for winter 2020, with the completion of the 12-month follow-up in winter 2021.

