### Strengths and Limitations

Previous research demonstrated that 8 weeks of Happify Health use improved subjective well-being among people with chronic physical conditions, including type 2 diabetes, at the same rate as people without these conditions [61]. However, the previous study examined the effects of Happify Health use on users with at least one self-reported chronic condition but was unable to examine the impact on users with specific chronic conditions. Therefore, this will be the first attempt to examine the effects of Happify Health use specifically on individuals with type 2 diabetes. Moreover, the previous study assessed only well-being, whereas this study will examine depressive symptoms and, more importantly, diabetes-specific outcomes such as HbA_1c_, frequency of self-care behaviors, and diabetes-related distress. Consequently, this study will provide a more comprehensive analysis of whether Happify Health use can improve physical health outcomes as well as psychological outcomes among individuals with poorly managed type 2 diabetes and elevated depressive symptoms.

This study also plans to include 3-, 6-, and 12-month follow-up assessments, providing important information about the longitudinal effects of this intervention. Longitudinal research on the impact of psychological interventions on people with diabetes remains limited [30], but research suggests that long-term follow-ups are important, as some effects may dissipate over time [30], whereas other effects may only emerge or become stronger over time [30,31].

Previous research has also been characterized by small samples, with sample sizes for in-person interventions ranging from 23 to 139 [30]. Sample sizes for research testing digital interventions have often been higher; however, most of these studies assessed only psychological well-being (depression and diabetes-related distress) and not physical health outcomes such as glycemic control [47]. Although the levels of attrition for long-term follow-up assessments are difficult to predict, based on response rates in previous RCT research using Happify Health ranging from 56% to 72% for 8-week interventions [60], our sample size postintervention is likely to be substantially higher than that in the previous studies. Given the mixed findings with glycemic control in previous research, it is important to examine these effects with larger samples to determine whether previous null findings are related to a lack of power.

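### Discontinuing the study at the 20% look could leave a null on about 40 to 59 HbA1c reports when, on reasonable calendar assumptions, more than half of the 400 are already randomised; closing enrolment and following those people would cost little

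*Protocol article*

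**What the plan says.** The Results section gives the reason for an early look, "Owing to the high cost associated with this research", and its timing: "we plan to conduct preliminary analyses once 20% of our target sample has completed the 8-week intervention". The consequence follows: "If we find no trends suggesting Happify Health use predicts primary outcomes, we plan to discontinue the study".

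On timing, the abstract says "Recruitment is expected to begin in June 2020" (the Results section says only the second quarter of 2020). Enrolment is rolling, in that "participants will begin the 8-week intervention as they are recruited and consent to participate in the study", and the same sentence group closes the 8-week phase "with an estimated intervention completion date for all participants in the fourth quarter" (the abstract says winter 2020). The Participants section continues recruitment until 400 are randomised. No pause at the look is mentioned.

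The Primary Outcome section and Table 1 place the first post-baseline HbA1c at week 12, 3 weeks after the intervention ends. The Strengths and Limitations section says: "Previous research has also been characterized by small samples, with sample sizes for in-person interventions ranging from 23 to 139". It adds that larger samples are needed to learn whether earlier null glycaemic results reflect low power.

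**The concern.** The look is labelled 20%, but that counts people who have finished 8 weeks. Others keep enrolling during those 8 weeks, so the share already randomised is much larger. The primary outcome is reported 3 weeks after the trigger, so the share with an informative HbA1c is smaller than 20%.

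Taken literally, a stop at that moment ends data collection on many people who are already randomised and owe only remote self-reports. The negative result would rest on a sample of the size the article itself criticises. The article's literature review also notes that HbA1c effects in some studies appeared only 1 to 3 months after the intervention. Those are the reports that a full stop would forgo.

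Whether the absence of a trend is a sound stopping criterion is a separate question. This point concerns only what happens to those already randomised.

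**Working it through.** The article states no share randomised at the look, so there is no figure to reproduce beyond 0.20 × 400 = 80 completers and the maximum compensation, 4 × 15 + 56 + 28 + 4 × 5 = US $164 per person (US $65,600 for 400).

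**Inputs from the article:** target 400; 80 completers; 1-week run-in before randomisation; 8-week intervention; 8-week response of 56% to 72% in earlier trials of the platform (reported, not adopted for planning).

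**Assumptions:** recruitment opens 1 June 2020; the last participant finishes on 31 December 2020; accrual is uniform; a completer is someone who responds at week 8, with probability *r*.

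**Randomisation window.** 1 June to 31 December is 213 days. Then 213 − 7 − 56 = 150 days, or *T* = 21.4 weeks. For a June start and fourth-quarter finish this is the longest window available, which makes the share at the look as low as it can be under uniform accrual.

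**Randomised at the look** = 80/*r* + 400 × 8/*T*. The second term is the number still inside their 8 weeks: 400 × 8/21.43 = 149.

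**HbA1c in hand at the look.** The first report falls 10 weeks after randomisation (week 12 minus week 2) or 11 weeks (8 + 3). The count is 400 × *r* × (*t* − 10 or 11)/*T*, where *t* = (80/*r*)/400 × *T* + 8 is the week of the look.

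**Respondents if everyone randomised is followed** = 80 + 149.3 × *r*, which applies the 8-week response rate to the HbA1c report.

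| *r* | 80/*r* | Look at week | Randomised | HbA1c in hand | Respondents if followed |
|---|---|---|---|---|---|
| 1 | 80 | 12.3 | 229 (57%) | 24–43 | 229 |
| 0.72 | 111 | 14.0 | 260 (65%) | 40–53 | 188 |
| 0.56 | 143 | 15.7 | 292 (73%) | 49–59 | 164 |

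**Precision.** For two equal arms and total *n*, the unadjusted 95% half-width in SD units is 1.96 × √(4/*n*):

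- *n* = 40: 0.62; *n* = 59: 0.51
- *n* = 164: 0.31; *n* = 188: 0.29

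**Sensitivity of the share randomised** (from no losses to 56% response, uniform accrual unless stated):

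- 30 June start, 31 December finish: 66% to 82%.
- 1 June start, 15 November finish: 74% to 90%.
- 1 June start, 1 October finish: 100%.
- 1 June to 31 December with linearly rising accrual: 67% to 94%.
- 1 April start (the second-quarter wording at its earliest), 31 December finish: 46% to 62%.
- 1 June start, with the abstract's winter 2020 stretched to 20 March 2021: 45% to 60%.
- Base calendar, but the look waits until 80 people have the week-12 HbA1c: 67% to 87%.

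**What a full stop saves.** On the base calendar at 72% to 56% response, at most about US $13,100 to 15,700 of the US $65,600 has been paid by the look, so 76% to 80% is unspent. Of that, US $17,700 to 22,900 belongs to people not yet randomised and US $29,700 to 32,200 to those already randomised.

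**What following those already randomised costs.** US $15 for the questionnaire plus US $5 for the HbA1c is US $20. For 260 − 80 = 180 to 292 − 80 = 212 people this is US $3,600 to 4,240, or 5.5% to 6.5% of US $65,600. The 21 to 40 completers still awaiting their HbA1c add US $5 each, at most US $200.

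**The case against.** A sponsor may end a study for cost, and the saving is real. A reader might infer that a stop saves little because so many are already randomised. The figures do not support that: about three-quarters or more of maximum compensation, twelve months of follow-up and the retention calls would be avoided.

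A reader might also infer that 65% to 73% is fixed by the protocol's own calendar. It is not. That band needs the start, finish, uniform accrual and response rates assumed above, and two looser calendars fall below half when losses are few.

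Nor does the article support saying that outcome data on most randomised participants would be thrown away. The 180 to 212 without a week-8 response include 31 to 63 who have already passed week 8 without responding. The expected gain in week-8 respondents is 84 to 108, or 29% to 42% of those randomised. Nor would a null rest on 80 people, since fewer than 80 would have the primary outcome.

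Finally, the article does not define discontinuation, and the full protocol may say how enrolled participants are handled. This stands as a limit on the point: the loss occurs only on the literal reading. But the sentence is a stated rule, not an omission. Just before it, the article speaks of continuing follow-up data collection, so ending the study reads most naturally as ending that collection. If only enrolment was meant, the proposed wording changes nothing in practice.

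**Conclusion.** The point holds in a limited form. With a June 2020 start, fourth-quarter completion and uniform accrual, more than half of the 400 would be randomised when the 20% look falls due, and about 149 would be partway through their 8 weeks. At 56% to 72% response only about 40 to 59 people would have the primary outcome. A literal full stop would then leave a null well inside the 23 to 139 range the article calls small. It would be too imprecise to separate absence of effect from lack of power, which is the question the article sets itself.

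Following those already randomised would narrow the half-width to about 0.29 to 0.31 SD, if 8-week response carries over to the HbA1c report. The half-widths ignore baseline adjustment and the planned hierarchical model, so they serve for comparison and do not forecast the trial's precision. The change is worth making because it is cheap and harmless on either reading of the sentence. Confidence is medium, since the accrual pattern and the meaning of discontinuation are not stated.

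**What to change.** In the Results section, replace discontinuing the study with closing enrolment. State that everyone already randomised will still be asked for the postintervention questionnaire and at least the week-12 HbA1c, and that the result will be reported on all of them. Add the number expected to be randomised at the look, with the accrual assumption behind it, so that the cost argument rests on that figure. Access to the app after a stop is a separate matter and is not addressed here.

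The cost is a sentence or two of text. After a stop it is about US $20 per person in compensation, roughly US $3,600 to 4,240 if everyone responds, plus some staff time. The paid daily ratings can be left optional. A stop would save slightly less than a full termination, but most of the saving would remain.
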